**Methods/Design:**

We will conduct a Randomised Controlled Trial (RCT) in which 160 children and adolescents aged 8–18 years are randomly allocated to cognitive behavioural *Grief-Help* or to a *supportive counselling* intervention; both treatments are combined with five sessions of parental counselling. We will recruit participants from clinics for mental health in the Netherlands. The primary outcome measure will be the severity of Prolonged Grief Disorder symptoms according to the Inventory of Prolonged Grief for Children (IPG-C). Secondary outcomes will include PTSD, depression and parent-rated internalizing and externalizing problems. Mediators like positive parenting and maladaptive cognitions and behaviours will be identified. We will also examine possible moderators including demographic variables (e.g. time since loss, cause of death), psychopathology symptoms in parents (PGD, anxiety and depression) and child personality. Assessments will take place in both groups at baseline, after the treatment-phase and three, six and twelve months after the post-treatment assessment.

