Given the need for effective therapy for PGD symptoms in children and adolescents, we developed a nine-session protocolized cognitive-behavioural treatment that is administered in combination with five sessions of parental counselling. This treatment is called *Grief-Help*. It is based on a cognitive-behavioural model of processes that interfere with adjustment to loss. Two pilot studies of this treatment have been done.

The first was a multiple-baseline study of six bereaved children and adolescents, which showed that the intervention coincided with reductions in symptoms of PGD, depression, PTSD and (parent-rated) internalizing and externalizing problems [21]. The intervention proved to be feasible, as both children and parents evaluated the treatment positively. That is, all participating children and parents gave favourable scores regarding their satisfaction with each session, the contact with their therapist and the information they received, attesting to the feasibility of this treatment approach. Results showed that after treatment there were reductions in symptoms of PGD, depression, posttraumatic stress and parent-rated internalizing and externalizing problems. Averaged across the six participants, reductions in scores on the outcome measures were all statistically significant, and all pretreatment to posttreatment effect sizes were large (Cohen’s *d* > 0.8).

The second pilot study was an open trial conducted with ten children and adolescents [22]. We conducted this study to evaluate the potential effectiveness of Grief-Help therapy among children confronted with losses other than the loss of a parent or sibling and to investigate whether the program is effective when the loss occurred more than 12 months prior to initiation of treatment. In this study, patients significantly improved from pretreatment to posttreatment, with large improvements observed in self-rated PGD and bereavement-related posttraumatic stress (effect size (ES) > 0.8) and small to moderate improvements in depression and parent-rated internalizing and externalizing problems (0.2 < ES < 0.8). Additional analyses focused on predictors of treatment outcomes suggested that Grief-Help therapy might be less effective for children and adolescents who are further removed in time from the loss and for those confronted with loss due to suicide. Taken together, Grief-Help therapy appears to be a promising treatment, and controlled evaluation is clearly indicated.

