### Other information

Demographic information will be assessed at baseline. Treatment adherence will be measured in terms of the number of sessions attended and completion of homework assignments. Adherence to both treatment protocols will be promoted by regular meetings with the therapist. Therapy sessions will be audiotaped, and randomly selected tapes will be discussed to ensure that therapists adhere to the protocols.

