### Statistical analyses

Most analyses will be conducted using the software program SPSS (SPSS, Inc, Chicago, IL, USA). Descriptive analyses will be carried out using standard methods. For analysis of the primary and secondary outcome measures, we will use analysis of covariance with the outcome measures posttreatment or at follow-up sessions as dependent variables, treatment condition as a factor and preintervention scores of the outcome variables as covariates. We will compare the scores of children in both groups with their own scores on previous assessments by using regression analysis and/or structural equation modelling. Mediator and moderator models will be tested. Analysis and reporting of the results will be carried out according to the CONsolidated Standards of Reporting Trials (CONSORT) 2010 Statement guidelines [52].

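### The outcome ANCOVA adjusts only for the preintervention score; prespecifying time since loss and loss by suicide as further covariates would be a cheap, modest refinement of a valid analysis

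*Protocol article*

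**What the plan says.** Statistical analyses (protocol article): the primary and secondary outcomes are analysed by ANCOVA. Condition is the factor, and the model takes "preintervention scores of the outcome variables as covariates". No further covariate is named. The same section says that mediator and moderator models will be tested.

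Background, on the earlier work: "The second pilot study was an open trial conducted with ten children and adolescents". Its additional analyses "suggested that Grief-Help therapy might be less effective for children and adolescents who are further removed in time from the loss". The article raises the same possibility about a second group, namely "for those confronted with loss due to suicide".

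Abstract, Methods/Design: the possible moderators include "demographic variables (e.g. time since loss, cause of death". Other information: "Demographic information will be assessed at baseline". Table 1 likewise places the demographic variables at A1, and Procedure and randomisation puts A1 before allocation.

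Trial objective and Discussion give time since loss and cause of death a role as moderators only. Procedure and randomisation describes random allocation to two conditions and mentions no stratification.

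**The concern.** Two variables that the sponsor's own pilot singled out are available before randomisation, but as written neither the allocation nor the main outcome model uses them.

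The planned moderator models do a different job. They ask whether the treatment effect varies with time since loss or cause of death. They do not reduce the residual variance behind the main between-arm comparison, and they do not adjust it if the arms happen to differ on these variables.

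Two things are at stake, both limited:

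- some precision, if the variables predict outcome beyond the baseline score;
- protection against a dispute, if an imbalance appears and covariates are then chosen with the results in view.

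**Working it through.** **Inputs from the article (Sample size).** 80 per arm, 20% dropout, effect size 0.50, α 0.05 with one-sided testing, power 0.80. Completers per arm: 80 × 0.80 = 64.

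**The plan's own figure.** A two-sample t-test at d = 0.50 and power 0.80 needs 51 per arm one-sided (51/0.8 = 63.75, so 64 recruited) or 64 per arm two-sided (64/0.8 = 80 recruited). The stated 80 therefore matches a two-sided calculation, not the stated one-sided one. That is a separate matter; here it only means that both versions are shown.

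**Assumptions, since the article gives no figures.**
- ρ, the correlation between baseline and outcome score: 0.5 (0.7 as a variant).
- R², the share of variance left after the baseline score that the two covariates explain: 0.02 to 0.15.
- Share of children bereaved by suicide: 5%, 10% or 20%.

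**Precision.** Residual SD = √((1 − ρ²)(1 − R²)). The standard error falls by 1 − √(1 − R²). Power is that of a t-test with 64 per arm and standardised effect 0.50/(residual SD).

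At ρ = 0.5 the baseline-only model has residual SD √0.75 = 0.866 and standardised effect 0.50/0.866 = 0.577.

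| R² | SE reduction | Power, two-sided | Power, one-sided |
|---|---|---|---|
| 0 (stated model) | – | 0.900 | 0.946 |
| 0.02 | 1.0% | 0.906 | 0.949 |
| 0.05 | 2.5% | 0.914 | 0.954 |
| 0.10 | 5.1% | 0.927 | 0.962 |
| 0.15 | 7.8% | 0.940 | 0.970 |

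At ρ = 0.7, one-sided power goes from 0.989 to at most 0.996.

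**Cost of two degrees of freedom.** With 128 completers the variance rises by about 2/125 = 1.6%, which the table leaves out. Net variance factor: at R² = 0.02, 0.98 × 1.016 = 0.996, almost no gain; at R² = 0.15, 0.85 × 1.016 = 0.864, a standard error about 7% lower. Break-even is at an R² of about 1.6%.

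**Chance imbalance.** Probability that the arms differ by 10 percentage points or more in loss by suicide (difference of two independent binomials):

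| Assumed share | 80 per arm | 64 per arm |
|---|---|---|
| 20% | 0.138 | 0.150 |
| 10% | 0.048 | 0.055 |
| 5% | 0.007 | 0.009 |

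If loss by suicide shifted the outcome by 0.5 SD (assumed), a 10-point imbalance would move the estimate by 0.10 × 0.5 = 0.05 SD, a tenth of the design effect of 0.50.

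**Strength of the pilot signal.** With n = 10, even an observed correlation of 0.5 has a 95% interval of tanh(0.549 ± 1.96/√7), that is −0.19 to 0.86.

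**The case against.** The strongest case against is that nothing here is an error. ANCOVA on condition and baseline score is a sound analysis of a randomised comparison: type I error is controlled, the estimate is unbiased over allocations, and the confidence interval already allows for chance imbalance. The article does not rule out further covariates, and a full analysis plan, not shown, may add them. All of this stands.

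A reader might infer that the plan ignores known predictors of outcome. The article does not support that. The evidence is a hedged remark from ten children in an open trial. With no control arm, that pilot could not separate a prognostic factor from an effect modifier. Its wording leans towards effect modification, and the planned moderator models are the direct response to that. A main-effect covariate would not replace them.

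A reader might also measure the gain from a power of 0.80. That figure belongs to an unadjusted two-sided t-test. The stated model already adjusts for the baseline score, so its power is higher and the added gain smaller.

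What the objection does not remove is that the two variables are already collected before allocation, are the natural candidates on the sponsor's own evidence, and cost almost nothing to include. Moderator models do not do that work for the main estimate.

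**Conclusion.** The point holds as a minor improvement, not as a defect. The stated ANCOVA is valid, and no bias or contradiction follows from its covariate set.

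The benefit depends on the two variables being prognostic beyond the baseline score, which the article does not establish. Over the assumed range the gain is at most about 4 power points two-sided and 2.4 one-sided at ρ = 0.5, and less at ρ = 0.7. At the bottom of the range the lost degrees of freedom nearly cancel it. A 10-point imbalance in loss by suicide is plausible only if such losses are common: about 14–15% of allocations at a 20% share, about 5% at 10%, and under 1% at 5%. The more dependable benefit is that naming the covariates in advance removes a later choice.

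**What to change.** Unless the analysis plan already does so, add a sentence to Statistical analyses that names time since loss (continuous) and loss by suicide (yes/no) as covariates beside the baseline score in the outcome ANCOVA. Fix this before any comparative result is seen; Trial status reports that recruitment is still under way. Report the baseline-only model as a sensitivity analysis and keep the moderator models as planned.

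Cost: one sentence and two degrees of freedom, with no new data and no change to randomisation or conduct. The downside is a slight loss of precision if the two covariates explain less than about 1.6% of the residual variance.

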### Protection of data privacy

Children and parents participating in this study will be assigned a number. This number will be used in the data set. Key lists of participants’ names and assigned numbers will be stored separately from the data in lockable cabinets and rooms and will be deleted after final data analyses. No conclusions will be drawn from the data on individual clients.

### Publication policy

We plan to publish the results of this study in peer-reviewed national and international journals. The results will be presented at national and international scientific conferences.

## Discussion

There is growing evidence that childhood PGD is a clinically significant condition [3,7]. However, there is limited knowledge about effective treatment interventions for children confronted with loss [11]. Given the lack of effective treatments for childhood PGD, research is urgently needed. Herein we have presented the protocol of a study designed to investigate the effectiveness of a novel cognitive-behavioural treatment called *Grief-Help* in comparison with supportive counselling for childhood PGD and to enhance knowledge about the variables mediating and moderating the effects of Grief-Help therapy. The current study is a randomised controlled trial among bereaved children and adolescents (ages 8 to 18 years) with elevated PGD who will be randomly allocated to one of the intervention groups. To the best of our knowledge, we are the first researchers to compare Grief-Help therapy with supportive counselling in bereaved children. In this study, we hope to contribute to the treatment of childhood PGD as well as to knowledge about mediators and moderators of change.

This study has several strengths. First, we will compare two different treatment conditions instead of a treatment and a waiting list condition. Both treatments are similar in certain aspects. Both treatments comprise nine sessions for the children and five sessions for the parents, and, in both conditions, children and parents will get the same psychoeducation. This will make it possible to evaluate different outcomes in terms of specific interventions, such as cognitive restructuring, exposure (both imaginary and *in vivo*), behavioural activation and confrontational writing. The second strength of this study is the fact that we will use validated measures. A third strength is that there will be multiple sources of information, because both parents and children will be administered multiple measures. Another strength is that, in this study, we will go beyond simple effectiveness questions and examine mechanisms that can explain the effects (for example, positive parenting, maladaptive cognitions and behaviours) and possibly moderate them (for example, demographic variables, time since loss, cause of death). By doing this, we will gain better insight into what works for whom.

The study also has potential weaknesses. First, it is possible that therapists (or someone else who does the intake interview in a specific setting) will be biased toward selecting children who are likely to benefit from treatment instead of including in A1 all children who meet the inclusion criteria. Second, only family members who are participants and receivers of treatment will be used as informants, without including more objective persons such as teachers.

## Trial status

Ethical approval for this study has been obtained from a medical ethics committee (Central Committee on Research Involving Human Subjects NL30528.041.09). All therapists have been trained at the different participating sites. Patient recruitment is ongoing and will continue until mid-2014.
